**BAY 43-9006 (NSC 724772) 400 mg po BID over 4 weeks.**

This dose may subsequently be reduced for individual patients, depending on toxicity (Section 5.2).

In order to study the effects of BAY 43-9006 on BRAF and on other components of the pathway, we will perform pretreatment and post-treatment tumor biopsies in the first 13 patients of each subgroup. The biopsies, which will be performed in the outpatient facility, will be either punch biopsies (6-8 mm diameter) or excisional biopsies performed by a surgical member of the Melanoma Disease Management team. The first portion of the biopsy will be used to evaluate the B-RAF status of the patient. Another portion of the tissue will be preserved in formalin and submitted to the NYU Department of Pathology. This material will be used to confirm the presence of melanoma and will be used for the immunohistochemical analyses of phospho-MAPK and cyclin D1 expression. The remaining portion will be trimmed of fat and excess connective tissue, and snap frozen in liquid N2. This material will be used for the Western blot analyses.

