**7.0 CORRELATIVE/SPECIAL STUDIES**

**7.1** *BRAF* exon 15 and *NRAS* exon 3 will be sequenced from paraffin-embedded melanoma tumor tissues by the [name]/ [name] lab at NYU. In our published study, 92% of mutations in metastatic melanoma tissues were in BRAF exon 15. BRAF exon 11 will not be examined before treatment because our study indicated that only (2/77) 2.6% of metastatic melanoma tissues harbor this mutation. (Cancer Res. 2003 Jul 15;63(14):3955-7.) NRAS will be assessed despite its relatively rare occurrence (exon 3 mutations were found in only 4% of tumors in our study) because it functions upstream of BRAF. Activating mutations in NRAS, therefore, may lead to an increase in the level of BRAF activity and may explain why a patient with a wild-type BRAF tumor would response to treatment with BAY 43-9006.

We expect tumors from 6 or 7 patients to harbor a *BRAF* mutation and tumors from 1 or 2 patients to harbor an *NRAS* mutation. We anticipate that 2-3 patients will have no detectable mutation in either of these genes.

Representative tumor tissue sections will be sent to the [name]/[name] laboratory at NYU via hand delivery or overnight mail to ensure timely delivery. Genomic DNA will be extracted from paraffin tissue blocks using a Qiagen Tissue Kit (Qiagen, Valencia, CA). Exon 3 of N-RAS and exon 15 of BRAF will be amplified by PCR and sequenced using the methods described in our published paper. Turn-around time is expected to be within 10 days of receipt of tumor samples. (**Appendix C**)

**7.2** Tumor levels of CDK4, phospho-MAPK, and cyclin D1 will be assessed by our newly optimized quantitative immunohistochemistry. Expression of p85 PI3 kinase (expected to be unaffected by treatment) will be assessed as internal controls. (**Appendix D**).

These studies will be done using the formalin-fixed portion of the biopsies. By utilizing quantitative immunohistochemistry to determine relative alterations in protein expression levels, we eliminate the need for handling and delivery of frozen tissue. In addition, we will measure phosphorylated MAPK by immunohistochemistry using an antibody to the activated,phosphorylated MAPK (Cell Signaling Technology, Beverly,MA). These studies will be done using the formalin- fixed portion of the biopsies. As a result, these analyses will not exhaust tissues required for the immunoblotting studies described above.(**Appendix D**)

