**11. STATISTICAL CONSIDERATIONS**

**11.1 Endpoints**

Primary endpoint:

- Response rate (RR)

Secondary endpoints:

- Time to progression (TTP)
- Toxicity
- Correlative Data
  1. **Study Design / Stratification Factors**

*Clinical Endpoints*

The primary endpoint of this trial is response rate defined as is either a complete or a partial response at the end of second cycle, using the RECIST criteria.

The response rate for standard of care DTIC is 5-10%. If the response is < 5%, the new treatment will not be considered for further study.

In each subgroup defined by BRAF status, a minimax two-stage Simon design will be used to test the null hypothesis that response rate at the end of second cycle (56 days) is p  0.05 versus the alternative that the response rate is p ≥ 0.20. If the drug is actually not effective, there is 3.3% probability of concluding that it is (the target was 5%). If the drug is actually effective there is a 14.2% probability of concluding that it is not (the target was 20%). After testing the drug on 13 patients per BRAF subgroup in the first stage, the trial will be terminated if 0 patients per subgroup respond. If the trial goes on to the second stage, a total of 37 patients per BRAF subgroup will be studied. If the total number responding is less than or equal to 4 patients per subgroup, the drug is rejected for that subgroup.

The overall response rate along with subgroup-specific response rates will be estimated at the end of the trial along with 95% confidence interval.

*Correlative Study Endpoints*

An important goal of this trial is to evaluate the biological markers pre and post treatment. Eligibility for the first stage of the trial (first 13 patients in each subgroup) requires that patients have biopsiable sites of disease. Tumor tissue will be collected and assessed for change in BRAF, P-MAPK, CDK4, and Cyclin D1 levels pre versus post treatment by analyzing the changes in the intensity of the specific bands on immunoblot. This is usually done visually (increase, no change, decrease) but can be quantified using a digital scanner. It is critically important to ensure that equal amounts of protein are loaded on to each lane. This can be confirmed by comparing the intensity of the p85 PI3k bands. The proportion of patients with decreases in levels of BRAF, CDK4, or phospho-MAPK will be estimated along with 95% confidence intervals.

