**Collection of samples**

# Tumor samples

Pre-treatment samples can be collected up to 2 weeks prior to starting treatment. The post-treatment sample should be collected 18-48 hours after the first treatment cycle. Although in some patients it will be possible to sample the same tumor pre-treatment and post-treatment, in most patients different tumors will be sampled. It is ideal to obtain multiple pre-treatment and post-treatment samples, an attempts will be made to carry this out.

The pre-treatment and post-treatment melanoma tumor samples will fixed in formaline and parffim embedded. Samples will be trimmed of obvious non-melanoma tissue. If there is a sufficient amount of normal skin associated with the sample, the normal skin may be stored separately and analyzed. Ideally, tumors biopsy will be approximately 1cm3. If larger samples are obtained, they will be split in duplicate. Blocks will be labeled with the patient’s name, protocol site (e.g NYU, Chicago university, Cornell ), date of collection, and an indication whether the sample was pretreatment or post-treatment.

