**APPENDIX F**

**Monitoring of Collagen Cryptic Epitopes in Serum and Urine:**

Standard ELISA methods have been used in the development of the cryptic collagen ELISA Assay. Briefly, Mabs HUI77 or HUIV26 are immobilized on 96-well microtiter plates. The plates are next washed with buffer and incubated with 5% BSA in PBS for 1.5 hours to block non-specific binding sites. Serum samples are diluted in 1:2 in dilution buffer and 50µl is added to each well and allowed to incubate for 2 hours at room temperature. The plates are next washed 8 times with wash buffer and incubated with a biotinylated polyclonal antibody to collagen for 2 hours. The plates are washed again and incubated with HRP-conjugated anti-Biotin antibody for 2 hours. Finally, the plates are washed and peroxidase substrate is added. The optical density is measured at a wavelength of 492 nm. Serum and urine will be collected for monitoring at day 6 of each cycle following treatment. The amount of denatured type IV collagen in ng/ml will be assessed.

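### The correlative pathway endpoint rests on contradictory tissue and assay instructions, and its proportion of decreases has no reference for decreases that arise without a drug effect

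*Protocol*

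**What the plan says.** Objective 1.4 is to determine, in the first 13 patients of each BRAF subgroup, whether treatment disrupts the pathway by depleting BRAF or downstream proteins.

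- **Section 11, Correlative Study Endpoints.** Change in BRAF, P-MAPK, CDK4 and cyclin D1 is assessed "by analyzing the changes in the intensity of the specific bands on immunoblot". On scoring: "This is usually done visually (increase, no change, decrease) but can be quantified using a digital scanner". The p85 PI3K band checks equal loading. The summary is: "The proportion of patients with decreases in levels of BRAF, CDK4, or phospho-MAPK will be estimated along with 95% confidence intervals". Cyclin D1 is assessed but is not in that summary. The same section adds IHC for cyclin D1 and phospho-MAPK, read visually as the percentage of positive cells.
- **Section 4.1.2.** After portions for genotyping and formalin, the rest of the biopsy is "snap frozen in liquid N2. This material will be used for the Western blot analyses".
- **Section 7.2.** CDK4, phospho-MAPK and cyclin D1 are measured by quantitative IHC with p85 as internal control, and "we eliminate the need for handling and delivery of frozen tissue". The same section then says that this work spares the tissue needed for immunoblotting.
- **Appendix C, Tumor samples.** "The pre-treatment and post-treatment melanoma tumor samples will fixed in formaline and parffim embedded". It also says that "in most patients different tumors will be sampled".
- **Appendix D.** IHC is quantified by image analysis as summed staining intensity.
- **Appendix F.** "Serum and urine will be collected for monitoring at day 6 of each cycle following treatment". The section 8 calendar places collagen epitopes on D1 and D28.

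**The concern.** There are two problems with objective 1.4. First, a site that follows Appendix C would have no frozen material for the assay on which section 11 relies. Tissue already fixed cannot be turned back into frozen tissue, and BRAF protein has no IHC fallback.

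Second, a bare proportion of decreases is hard to read. When the two biopsies come from different lesions, ordinary lesion-to-lesion variation produces decreases and increases with no drug effect at all. The protocol gives no threshold for a decrease, no reference rate, and no clear statement on whether the three proteins are reported separately or pooled through the word *or*. A proportion that looks favourable could be mistaken for evidence of pathway inhibition.

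A separate problem affects objective 1.5. Collagen epitopes are to be related to tumour burden, but one of the two sampling instructions falls on a day with no tumour measurement.

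**Working it through.** **1. The plan's own figures.** None is stated for the pathway endpoint. The only operating characteristics in section 11 belong to the primary two-stage design (3.3% and 14.2%). Exact recalculation gives 3.29% and 14.17%, so they reproduce, and they are not in question here.

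**2. Tissue and assay instructions side by side.**

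| Place | Tissue | Assay and markers |
|---|---|---|
| 4.1.2 | Formalin portion plus frozen remainder | IHC: phospho-MAPK, cyclin D1; Western blot on frozen tissue |
| 7.2 | Formalin-fixed portion; frozen handling eliminated, yet immunoblot tissue assumed | IHC: CDK4, phospho-MAPK, cyclin D1, with p85 |
| Appendix C | Fixed and embedded; no frozen portion named | none stated |
| Appendix D | Fixed sections | IHC intensity by image analysis: cyclin D1, phospho-MAPK, phospho-ERK |
| Section 11 | Not stated | Immunoblot: BRAF, P-MAPK, CDK4, cyclin D1; IHC percentage of positive cells: cyclin D1, phospho-MAPK |

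BRAF protein appears only under immunoblot. IHC is a visual percentage in section 11 and a summed intensity in Appendix D.

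**3. Decreases with no drug effect (assumption).** Let *u* be the share of no-change readings. If lesion differences are symmetric, the chance of a decrease in one marker is p = (1 − u)/2. With u = 1/3, p = 1/3; with u = 0, p = 1/2. A larger *u* gives a smaller p. The protocol gives no value, so 1/3 to 1/2 is illustrative.

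For a decrease in at least one of three markers:
- fully correlated markers: p itself, so 33% to 50% (4.3 to 6.5 of 13 patients);
- independent markers: 1 − (1 − p)³, so 1 − (2/3)³ = 70.4% to 1 − (1/2)³ = 87.5% (9.1 to 11.4 of 13).

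**4. What the confidence interval can exclude (exact Clopper-Pearson, 95%).**

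| Result | Interval |
|---|---|
| 7/13 (54%) | 25.1% to 80.8% |
| 9/13 (69%) | 38.6% to 90.9% |
| 10/13 (77%) | lower limit 46.2% |
| 11/13 (85%) | 54.6% to 98.1% |
| 13/13 | lower limit 75.3% |
| 19/26 (73%) | 52.2% to 88.4% |
| 26/26 | lower limit 86.8% |

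One marker needs 11/13 (or 19/26 with the subgroups combined) to exclude 50%, and 9/13 to exclude 1/3. The probability of reaching 11/13 is 20%, 50% or 87% when the true decrease rate is 70%, 80% or 90%. On the pooled reading with p = 1/2 and independent markers, even 13/13 or 26/26 does not exclude 87.5%.

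**5. Decreases against increases.** If no-change readings are set aside, symmetric lesion variation gives a null of exactly 1/2 whatever *u* is. With 6 informative pairs all 6 must be decreases; with 8, all 8; with 10, at least 9; with 13, at least 11. Five pairs cannot exclude 1/2. Section 3.1.1 now admits patients without accessible lesions, so fewer than 13 pairs per subgroup is possible.

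**6. Collagen epitopes.** Appendix F specifies serum and urine on day 6 of each cycle. The calendar specifies D1 and D28, which are also tumour-measurement days, and lists neither a day-6 visit nor urine.

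**The case against.** The strongest reply is that these are secondary, exploratory data, analysed descriptively, with no decision resting on them. A proportion with an interval is a legitimate summary for that purpose, and finer analysis detail may sit in a SAP that is not at hand. This stands as a limit on severity. It does not excuse sections that give sites different instructions, or a summary that the protocol itself fixes without a reference.

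Several stronger readings are tempting, and the documents do not support them.

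- *There is no tissue for the immunoblots.* Section 4.1.2 reserves a frozen portion, and section 7.2 refers to a fixed portion rather than all tissue. What the documents show is a contradiction.
- *The endpoint cannot show that the drug acts.* Read marker by marker, 11/13 would exclude 50%, although systematic differences between the lesions chosen before and after could still confound it.
- *An inert drug gives 50%, or 87.5%, decreases.* Both figures are assumptions. The second also needs independence among proteins of one pathway read from the same specimens, and pooling. The plural intervals in section 11 fit one estimate per marker at least as well.
- *Scoring is purely visual and lesions are always unmatched.* A scanner is allowed, and Appendix C says multiple samples at each time will be attempted.
- *Objective 1.5 cannot be met.* The calendar already pairs epitopes with tumour measurements; only the Appendix F wording conflicts.

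**Conclusion.** The point holds as one of inconsistent specification and a missing reference. The protocol gives incompatible accounts of tissue handling, leaves BRAF protein dependent on frozen tissue that Appendix C does not provide, and scores IHC in two ways. The proportion of decreases does not by itself separate a drug effect from chance or lesion-to-lesion variation.

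The size depends on assumptions that the protocol does not settle. With 1/3 to 1/2 per marker, the background rate for any of three markers lies between 33% and 88%, according to how strongly the markers are correlated. For a single marker at n = 13, only 11 or more decreases exclude 50%. The Appendix F conflict is separate and smaller. The matter should be corrected, but the primary response analysis does not depend on it.

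**What to change.** 1. Before further biopsies, make sections 4.1.2, 7.2, 11 and Appendix C agree on tissue handling. Either retain a frozen portion, or remove BRAF protein from objective 1.4 and section 11.
2. Choose one IHC scoring method and state it in both section 11 and Appendix D.
3. Report each marker separately, cyclin D1 included, from the quantitative values already planned: the paired log(post/pre) relative to p85 PI3K, with a 95% CI. Add a sensitivity analysis restricted to same-lesion pairs. Immunoblot can remain as the complementary technique if frozen tissue is kept.
4. If the categorical proportion is kept, define a decrease, report it per marker, and compare decreases with increases by a sign test. Testing all patients against 50% is the wrong reference when no change is a category.
5. Align Appendix F with the D1 and D28 calendar days, and state whether urine is collected.

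The cost is minor protocol wording and some analysis work. The quantitative IHC and the p85 control are already planned, so no extra biopsies or visits are needed.

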**11.3 Sample Size/Accrual Rate**

A total sample size of 37 eligible patients per subgroup is planned. Accrual of 4-5 patients per month is expected, so that the study should be completed in, at most, 24 months.

**11.4 Analysis of Secondary Endpoints**

All patients will be followed for progression and survival. Kaplan-Meier estimates will be calculated for time to progression and overall survival, and medians, along with two-sided 95% confidence intervals, will be reported.

All adverse events without regard to causal relationship and by causal relationship to study drugs will be summarized.

Exploratory analyses of correlative endpoints will be examined over time using descriptive statistics and graphical displays. In particular, these endpoints will also be explored in relation to response to treatment and tumor burden.

**11.5 Reporting and Exclusions**

**11.5.1 Toxicity**

All patients will be evaluable for toxicity from the time of their first treatment with BAY.

- - 1. **Evaluation of response**

All patients included in the study must be assessed for response to treatment, even if there are major protocol treatment deviations or if they are ineligible. Each patient will be assigned one of the following categories: 1) complete response, 2) partial response, 3) stable disease, 4) progressive disease, 5) early death from malignant disease, 6) early death from toxicity, 7) early death because of other cause, or 9) unknown (not assessable, insufficient data). [Note: By arbitrary convention, category 9 usually designates the “unknown” status of any type of data in a clinical database.]

All of the patients who met the eligibility criteria should be included in the main analysis of the response rate. Patients in response categories 4-9 should be considered as failing to respond to treatment (disease progression). Thus, an incorrect treatment schedule or drug administration does not result in exclusion from the analysis of the response rate. Precise definitions for categories 4-9 will be protocol specific.

All conclusions should be based on all eligible patients. Descriptive analyses will also be provided for patient subsets that exclude patients for whom major protocol deviations have been identified (e.g., early death due to other reasons, early discontinuation of treatment, major protocol violations, etc.). The reasons for excluding patients from the analysis should be clearly reported.

# APPENDIX A

**ELIGIBILITY CRITERIA**

| Confirmed Stage IV Melanoma |  |
| --- | --- |
| Measurable Disease |  |
| No prior therapy |  |
| Tumor amenable to biopsy |  |
| Scans within 4 weeks |  |
| ECOG Performance Status 0-2 |  |
| ANC > 1.5 x 109/l |  |
| Platelets > 100 x 109/l |  |
| Total Bilirubin < 2 x ULN |  |
| AST/ALT < 2.5 x ULN |  |
| Creatinine < 1.5 x ULN |  |
| No Brain Mets or Stable Brain Mets for at least 6 weeks after whole brain radiation |  |
| Not pregnant |  |
| No uncontrolled medical illnesses |  |
| Signed informed consent |  |

**Appendix B**

**Performance Status Criteria**

| **ECOG Performance Status Scale** | | **Karnofsky Performance Scale** | |
| --- | --- | --- | --- |
| Grade | Descriptions | Percent | Description |
| 0 | Normal activity. Fully active, able to carry on all pre-disease performance without restriction. | 100 | Normal, no complaints, no evidence of disease. |
| 90 | Able to carry on normal activity; minor signs or symptoms of disease. |
| 1 | Symptoms, but ambulatory. Restricted in physically strenuous activity, but ambulatory and able to carry out work of a light or sedentary nature (e.g., light housework, office work). | 80 | Normal activity with effort; some signs or symptoms of disease. |
| 70 | Cares for self, unable to carry on normal activity or to do active work. |
| 2 | In bed <50% of the time. Ambulatory and capable of all self-care, but unable to carry out any work activities. Up and about more than 50% of waking hours. | 60 | Requires occasional assistance, but is able to care for most of his/her needs. |
| 50 | Requires considerable assistance and frequent medical care. |
| 3 | In bed >50% of the time. Capable of only limited self-care, confined to bed or chair more than 50% of waking hours. | 40 | Disabled, requires special care and assistance. |
| 30 | Severely disabled, hospitalization indicated. Death not imminent. |
| 4 | 100% bedridden. Completely disabled. Cannot carry on any self-care. Totally confined to bed or chair. | 20 | Very sick, hospitalization indicated. Death not imminent. |
| 10 | Moribund, fatal processes progressing rapidly. |
| 5 | Dead. | 0 | Dead. |

**Appendix C**

**Summary of Studies in Support of Genetic and Pharmacodynamic Endpoints:**

[figure not shown]

**Figure 1. BRAF HotSpot Mutation.** An electropherogram demonstrating the T1796A nucleotide substitution detected in a metastatic melanoma tissue sample.

The laboratories of [name] and [name] at NYU Medical center have recently reported on a series of analyses of *BRAF* and *N-RAS* mutations in 77 metastatic melanoma tumor specimens, and 11 melanoma cell lines1 (Cancer Res 63: 3955-3957, 2003, see Appendix II). In this study they amplified and sequenced *BRAF* exons 11 and 15, and *N-RAS* exons 2 and 3. They were able to detect mutations in 36 of 77 (47%) tissue specimens and 8 of 11 (73%) cell lines. Ninety-two percent of mutations in tissues occurred in *BRAF* exon 15, and 31 of 33 (94%) while exon 15 mutations consisted of the previously identified T1796A nucleotide substitution. An example of this mutation is shown in Figure 1.

In other preliminary studies, Drs. [name] and [name] have developed a PCR amplification strategy that specifically amplifies the T1796A mutant. They have designed three different oligonucleotide primers specific for the mutation (mFwd, mRev1, mRev2). These mutant specific primers are used with intronic primers to amplify products that range in size from 151 bp to 172 bp. Our colleagues had established the specificity of all three of the mutant-specific primers by testing them on melanoma cell lines SK-MEL 85 (wild-type for exon 15, mutant for exon 11), and SK-MEL 29 (mutant for exon 15). As shown in Figure 2, PCR reactions using each primer set were performed at annealing temperatures of 58oC, 60oC, and 63oC. Each primer showed specificity for the mutant product, as evidenced by disappearance of the wild-type band as the temperature increased (compare lanes 1, 4, and 7 (mutant) with lanes 2, 5 and 8 (wild-type). As part of the clinical study validation protocol the assay will be optimized for the assessments in tumor tissues along with peripheral blood nuclear cells.

58oC60oC 63oC

12345678 9M

400bp

200bp

100bp

261bp

168bp

261bp

172bp

**Figure 2. Multiplex PCR for mutant BRAF and p53 exon 4 (internal control).** DNA from SK-Mel 29 (BRAF mutant), lanes 2, 5, 8 or SK-Mel 85 (BRAF wild-type), lanes 3, 6, 9 was used as template to test the three mutant specific primers at 3 different annealing temperatures (Ta). Lanes 1-3, Ta=58oC; 4-6, Ta=60oC; 7-9, Ta=63oC. Each panel shows the result from a different primer. A. mRev2, B. mRev1, C. mFwd. In all three panels, the lower band is the product of the BRAF primers, the upper band, the p53 primers. Lanes 1, 4, and 7 are negative controls in which only the template DNA was omitted from the reaction.

[figure not shown]

[figure not shown]

[figure not shown]

**A**

**B**

**C**

Additional confirmation of the specificity of these primers will be obtained by analyzing a series of 9 other melanoma cell lines available in [name] laboratory. In addition, the utility of the assay will be extended further with the use of fluorescently labeled intronic primers that should enhance the sensitivity and specificity. Our collaborators estimate that fluorescent detection of PCR products will be approximately 200-fold more sensitive than detection using ethidium bromide-stained agarose gels. An example of this point is demonstrated in Figure 3 where serial dilutions of a fluorescently labeled PCR product were analyzed in an ethidium bromide-stained agarose gel and compared with the ABI 310 Genetic analyzer. Quantitation of the PCR products in the agarose gel using a molecular mass ladder showed that reliable detection of the PCR products was far superior using the ABI 310 analyzer compared to the agarose gel.

[figure not shown]

[figure not shown]

20ng

10ng

0.1ng

Figure 3. Sensitivity detection of PCR products using ethidium bromide stained agarose gels vs. an ABI 310 Genetic Analyzer. **Dilutions of fluorescently tagged PCR products from a tumor sample heterozygous for the microsatellite marker D9S2136 were analyzed using a 1.5% agarose gel (top panel) and ABI 310 Genetic Analyzer (bottom panel). Reliable detection in agarose is limited to amounts of 20ng or greater, whereas the sample shows peaks at 3 times baseline at 0.1ng, a 200-fold improvement in detection.**

